### Hypotheses and expected results

The PE would be constituted by a larger symptom improvement from Sequence 1 to Sequence 2 in the “medication” Instruction, than in the “control/placebo” Instruction (“medication”(S2-S1)>“control”(S2-S1). This is a general test of the efficacy of the placebo paradigm, which is a crucial building block for assessing the effect of the different Metaphors.

The design does not strictly permit the establishment of equivalence between Metaphors in the sense of a non-inferiority trial, which is deemed too ambitious at this stage. For the proposed protocol, a non-significant difference between VEx and HEx would be considered as a first step to establish the viability of the VEx (HEx = VEx). On a descriptive level, we are expecting a slightly lower effect induced by the VEx, but lower variance than under the HEx, amounting to comparable effect sizes. Beyond that, it is hypothesized that the audio/text Metaphor induces a smaller symptom improvement than the other conditions (HEx = VEx > audio/text) due to absence of visual social cues.

Using a more fine grained analysis at the Trial level could yield additional information, such that groups differ in early or late Trials only, or that the slope (pain changes in consecutive Trials) is different between groups. For example, a significant difference between “medication” vs. “control” could come about by a shallower pain increase in consecutive Trials in Sequence 2, despite identical initial sensitivity (see Fig. 4).

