**Fig. 4 Fig4:**
[figure not shown]
Possible results on the Trial level during Sequence 2 (post-intervention): Lower pain increase within the “medication” group (*dashed line*) vs. the “control” group (*solid line*)

If we indeed do not find significant differences of PEs induced by the VEx versus an HEx, we will proceed to more complex protocols (see “Potential and outlook”). If we do find differences such that an HEx proves superior to the VEx, we will return to the design phase and address weaknesses in the VEx software in an iterative design-test protocol until we can reliably elicit PEs using the VEx that are of comparable size with those elicited by an HEx.

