### Pilot study 2: evaluation of the pain protocol

To characterize the pain protocol (see above) and estimate reproducibility across Sequences (including possible carry-over effects like habituation and sensitization), we conducted a pilot study with only a waiting period between the two Sequences. All means are provided with standard deviations; significance testing was performed with hierarchical linear model analysis, cf. “Analysis and sample size estimation” (a more in-depth discussion is beyond the scope of this article). In this study, we included 33 healthy participants (21 female, 12 male; age 20.1 ± 2.4). Continuous pain ratings almost invariably increased within Sequences/between Trials. On average, participants showed substantial amounts of pain in both Sequence 1 (VAS 46.4 ± 15.0, range 23.5 to 83.6) and Sequence 2 (VAS 40.8 ± 15.5, range 18.8 to 78.8), with normal distributions on both occasions. These means constitute a slight but significant overall decrease in pain between the two Sequences. Conversely, single retrospective ratings show no difference for intensity (VAS 53.8 ± 17.7 versus 52.6 ± 21.1) and unpleasantness (VAS 55.9 ± 17.1 versus 55.6 ± 21.3).

The continuous ratings exhibited good reproducibility (intraclass correlation coefficient(2,1) *ρ* = .72) between the two Sequences, comparable to that of the retrospective ratings of intensity (*ρ* = .77) and unpleasantness (*ρ* = .68).

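### The audio/text hypothesis and the Metaphor ordering are worded on total symptom improvement, whereas the protocol defines, and acts on, the placebo effect

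*Protocol article*

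**What the plan says.** The Background section limits the PE to the part of symptom improvement that runs through expectancy about the treatment, and separates it from other sources of change. The section *Hypotheses and expected results* makes this operational: "The PE would be constituted by a larger symptom improvement from Sequence 1 to Sequence 2 in the “medication” Instruction", compared with the control Instruction. It calls that test one "which is a crucial building block for assessing the effect of the different Metaphors".

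Three statements about the Metaphors follow in the same section:

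- On VEx versus HEx, "a non-significant difference between VEx and HEx would be considered as a first step to establish the viability of the VEx". The sentence does not say in what quantity the difference is taken.
- On audio/text, "it is hypothesized that the audio/text Metaphor induces a smaller symptom improvement than the other conditions (HEx = VEx > audio/text". The quantity is symptom improvement, and no Instruction contrast is mentioned.
- The closing decision rule begins "If we indeed do not find significant differences of PEs induced by the VEx versus an HEx" and, if the HEx proves superior, sends the software back to design until it yields "PEs using the VEx that are of comparable size with those elicited by an HEx". Here the quantity is the PE.

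The Procedure section gives the main outcome as pain change at retest compared between groups, with random assignment to six Metaphor-by-Instruction groups. The article nowhere names Metaphor x Instruction as the test of a Metaphor hypothesis.

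**The concern.** Metaphor is the encounter itself, so it may change later pain by routes other than belief in the pill: calm, mood, distraction, novelty. The article allows for some of this. The Background mentions virtual reality as an analgesic distraction technique, and Limitations says novelty could strengthen or weaken effects. The *inert* Instruction within each Metaphor allows such influences to be subtracted. A Metaphor comparison on total improvement does not subtract them.

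The audio/text condition is included to gauge what visual social cues add beyond the verbal content. If it is compared on total improvement, a Metaphor that relaxes people equally under both Instructions could be credited with a larger PE. A real PE difference could also be masked by a shift in the opposite direction.

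**Working it through.** **1. What each contrast estimates.** Compare two Metaphors with equal cells. Let b be the difference in improvement present under both Instructions and D the true difference in PE. The Metaphor difference is then b in the *inert* cells and b + D in the *medication* cells.

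- Pooled over Instruction: [(b + D) + b]/2 = b + D/2
- *Medication* cells only: b + D
- Metaphor x Instruction on change: (b + D) - b = D

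Only the third matches the article's definition of the PE and its decision rule. A change over time common to all Metaphors drops out of all three.

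**2. Inputs.** *Analysis and sample size estimation* takes N = 50 from a rule of thumb and 15% attrition to reach 58 (50 x 1.15 = 57.5; dividing instead, 50/0.85 = 58.8). The article gives no effect size, alpha or power for this. I use N = 50, so 50/6 = 8.33 per cell. Pilot study 2 gives SDs of 15.0 and 15.5, means of 46.4 and 40.8, and ICC(2,1) = .72, with 33 participants. Two-sided alpha 0.05, 80% power and the normal approximation are my assumptions.

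**3. SD of the change.** SD² = 15.0² + 15.5² - 2r(15.0)(15.5) = 465.25 - 465r.

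- Using the ICC as the correlation, r = .72: SD = √130.45 = 11.42.
- Solving for r from ICC(2,1), which also penalises the mean shift of 5.6: r = .764 and SD = 10.49. Check: 2 x 177.6 / (465.25 + 31.4 - 3.3) = .72.

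**4. Standard errors and detectable differences at N = 50** (detectable = 2.80 x SE)

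| Contrast | Estimates | SE formula | SE (VAS points) | Detectable |
|---|---|---|---|---|
| Pooled | b + D/2 | SD√(1/8.33) | 3.6-4.0 | 10.2-11.1 |
| *Medication* only | b + D | SD√(2/8.33) | 5.1-5.6 | 14.4-15.7 |
| Interaction | D | SD√(4/8.33) | 7.3-7.9 | 20.4-22.2 |

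**5. Significant results when the PEs are equal (D = 0)**

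| Assumed b | Pooled | *Medication* only | Interaction |
|---|---|---|---|
| 5 points | 24-28% | 15-16% | 5% |
| 10 points | 72-79% | 43-49% | 5% |

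Example: with b = 5 and SE 3.96, 5/3.96 = 1.26, and P(Z > 1.96 - 1.26) is about 24%.

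**6. Does pooling buy power for D?** No. With b = 0 the pooled contrast carries D/2 on half the standard error, so its ratio of signal to SE equals that of the interaction. For D = 10 both have 24-28% power. The *medication*-only contrast is more precise for D, but only if b is taken to be zero.

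**The case against.** The strongest reply is that the phrase is shorthand. The paragraph before it defines the PE as a larger symptom improvement under one Instruction and says the Metaphor assessment builds on it. The stated aim is the VEx's efficacy in inducing PEs, and nothing says that Metaphors will be averaged over Instruction. Both Instructions are randomised within every Metaphor, so the right contrast can be estimated, and a fuller plan may specify it. This has force: the text supports saying that a non-placebo effect could be read as a PE, not that it will be. It does not remove the mismatch, because an analysis that followed the sentence literally would test a different quantity.

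A reader might also infer more than the document supports:

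- *That all the Metaphor hypotheses are on the wrong quantity.* The VEx-versus-HEx sentence leaves its quantity open, and the decision rule is explicitly on PEs. The clear fault lies in the audio/text hypothesis and in the ordering, which repeats HEx = VEx.
- *That Pilot study 2 shows the bias.* The pilot reports that "These means constitute a slight but significant overall decrease in pain between the two Sequences", a fall of 46.4 - 40.8 = 5.6 points with waiting only. A natural course common to all randomised groups cancels between Metaphors. It is neither evidence of b nor a guide to its size.
- *That a true PE difference is always halved.* This holds only when Instruction is averaged over.

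The mechanisms for b are plausible but unquantified. The encounter takes place in a separate room between the Sequences, so distraction during immersion is not implied. Mood and anxiety are measured as covariates, and novelty is to be examined as a moderator. These steps help, but they reach only what is measured; the randomised *inert* cells remove any shift common to both Instructions.

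**Conclusion.** The point holds as a mismatch of quantities: the audio/text hypothesis and the ordering HEx = VEx > audio/text are stated on total improvement, against the article's own PE definition and its decision rule. Tested as worded, the comparison estimates b + D/2 or b + D and not D. The algebra is exact for equal cells. The error rates in the working depend on assumed values of b, on a change SD derived from the pilot, and on the assumed alpha; the article gives no estimate of b.

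The document does not show that the *inert* cells will go unused, or that a false PE claim will result.

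Putting the question on the right quantity also shows how little N = 50 can say about it. Around an observed VEx-HEx difference in PE of zero, the 95% interval would reach about 1.96 x 7.27 = 14 to 1.96 x 7.91 = 15.5 points either way, against a pilot baseline mean of 46.4. The article concedes that it cannot establish equivalence; the decision to proceed after a non-significant result should be read in that light.

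**What to change.** 1. Reconcile the statements by putting all Metaphor hypotheses on the PE. For each Metaphor, PE = improvement under *medication* minus improvement under *inert*; the hypothesis becomes PE(HEx) = PE(VEx) > PE(audio/text).
2. Name the test: the Metaphor x Instruction x Sequence contrasts in the hierarchical model.
3. Report Metaphor differences within the *inert* cells separately, as non-placebo effects of the encounter.
4. Report the VEx-HEx difference in PE with its confidence interval, and describe a non-significant result as weak evidence of similarity.

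No new data are needed; the change is to the wording of the hypotheses and the contrast. The price is precision: the standard error is twice that of the pooled contrast, and the detectable difference is about 20-22 VAS points at N = 50 (18.9-20.6 if all 58 were evaluable), under the assumed alpha and power. Relative to pooling, no power for a PE difference is lost. Relative to a *medication*-only comparison precision is lost, but that comparison is valid for the PE only if b is zero.

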**Fig. 4 Fig4:**
[figure not shown]
Possible results on the Trial level during Sequence 2 (post-intervention): Lower pain increase within the “medication” group (*dashed line*) vs. the “control” group (*solid line*)

If we indeed do not find significant differences of PEs induced by the VEx versus an HEx, we will proceed to more complex protocols (see “Potential and outlook”). If we do find differences such that an HEx proves superior to the VEx, we will return to the design phase and address weaknesses in the VEx software in an iterative design-test protocol until we can reliably elicit PEs using the VEx that are of comparable size with those elicited by an HEx.

#### Current status

In the following, the development of the virtual experimenter is described in more detail. Furthermore, preliminary results from a pilot study pertaining to the VEx software are summarized (Pilot study 1). Finally, results from a pilot study pertaining to the pain protocol are summarized (Pilot study 2).

### Development of the stimulus material

The design of the VEx “[name]” (cf. Fig. 1) was informed by a preliminary survey including eight different photographs of supposed study physicians. Photographs were rated by a non-random sample (*N* = 10) on various dimensions (e.g., appearing competent and empathetic [44], trustworthy, believable, and enthusiastic [1, 18]) (data not shown).

The VEx prototype was modeled using MakeHuman version 1.0.1 and Blender version 2.69 (Blender Foundation, Amsterdam, Netherlands). It is rendered in a Unity 5.1.1 framework (Unity Technologies, San Francisco, CA, USA) on a 60“ screen display with 3D-capabilities. Lip-synchronization was performed using faceshift (faceshift, San Francisco, CA, USA). The software also includes an interaction module, which enables participants to ask the VEx a number of questions using a second 17” touch-screen display. Voice recognition is performed via the Microsoft Kinect (Microsoft, Redmond, WA) and processed using the Kinect Software Development Kit 1.8 (Microsoft, Redmond, WA) within the Unity framework rendering the VEx.

### Pilot study 1: evaluation of the virtual experimenter

This study was aimed at informing the direction of further development of the VEx, by investigating how the VEx prototype is perceived by random participants. The study protocol outlined above will employ a version of the piloted prototype once all changes according to the findings of this study have been integrated.

In this pilot study, 48 participants (23 female, 25 male; age mean ± SD 20.2 ± 2.3) watched the VEx instruction without actually undergoing the pain protocol, or receiving the presumed medication. Participants judged the VEx on an Expectancy Induction Characteristics questionnaire assessing dimensions considered conducive to placebo responses (e.g. [1, 18, 19]). The Expectancy Induction Characteristics questionnaire was constructed in our lab and consists of 11 items (semantic differentials). The items are subsumed in three scales pertaining to how convincing a person is perceived (scale Message), how likeable (scale Likeable), and how compelling (scale Compelling). The scales exhibit decent reliability with Cronbach’s alpha of .82, .68 and .82, respectively.

Results are presented in Fig. 5. While the VEx was judged favorably on the Message and Likeability scales, it received comparatively bad rating on the Compelling scale. We believe this to be owed to a rather neutral demeanor (both in verbal and nonverbal content) displayed by the model, which has been intentional to establish a solid baseline of the VEx’s efficacy. However, we are currently in the process of improving ratings in this scale by implementing higher behavioral realism (e.g. breathing, pre-recorded eye blinks) and a more animated presentation (e.g. more inflections during speech, more pronounced facial expressions).

**Fig. 5 Fig5:**
[figure not shown]
Rating (in percent) of the virtual experimenter simulation along 11 semantic differentials. Bars with thick borders display the scale means (*white* = Message, *light grey* = Likeability, *dark grey* = Compelling) composed of the items directly above

### Pilot study 2: evaluation of the pain protocol

To characterize the pain protocol (see above) and estimate reproducibility across Sequences (including possible carry-over effects like habituation and sensitization), we conducted a pilot study with only a waiting period between the two Sequences. All means are provided with standard deviations; significance testing was performed with hierarchical linear model analysis, cf. “Analysis and sample size estimation” (a more in-depth discussion is beyond the scope of this article). In this study, we included 33 healthy participants (21 female, 12 male; age 20.1 ± 2.4). Continuous pain ratings almost invariably increased within Sequences/between Trials. On average, participants showed substantial amounts of pain in both Sequence 1 (VAS 46.4 ± 15.0, range 23.5 to 83.6) and Sequence 2 (VAS 40.8 ± 15.5, range 18.8 to 78.8), with normal distributions on both occasions. These means constitute a slight but significant overall decrease in pain between the two Sequences. Conversely, single retrospective ratings show no difference for intensity (VAS 53.8 ± 17.7 versus 52.6 ± 21.1) and unpleasantness (VAS 55.9 ± 17.1 versus 55.6 ± 21.3).

The continuous ratings exhibited good reproducibility (intraclass correlation coefficient(2,1) *ρ* = .72) between the two Sequences, comparable to that of the retrospective ratings of intensity (*ρ* = .77) and unpleasantness (*ρ* = .68).

## Discussion

### Challenges

The two core challenges are the establishment of PEs in a tightly controlled protocol with only limited “dosing” of the placebo manipulation, and achieving a sufficient comparability of the VEx with the HEx interaction as to mimic the psychosocial effects necessary for PEs to arise. The placebo manipulation only contains a verbal expectancy manipulation comparable to those used in other placebo experiments (e.g. [5]). However, we chose to limit emphasis and enthusiasm on the side of the experimenter as much as possible, as to introduce as few as possible confounding factors at this point. This may mean that the PE will not be pronounced.

With the VEx, the greatest challenge is to create a sufficient rapport between him and the participant to be perceived as a social situation. The Ethopoeia concept [45] posits a substrate neutrality of human versus virtual agent behavior: as long as social cues are displayed, they will lead to “mindless responses” [45], p. 83). However, these cues go beyond the behavioral realism of the display (e.g. facial expressions, gestures, blinking, breathing) – which is necessary but not sufficient [46] – and extent to interactional components to attribute agency to the virtual agent, such as turn-taking, visual attention to interlocutors, and behaviors reducing inter-personal distance. While technology like the “rapport agent” exists [47, 48], which has been tailored to naturally engage humans in conversation, our VEx software does not yet exhibit the same capabilities. At this stage, the VEx includes an FAQ module, engaging participants to ask questions with prerecorded answers; furthermore, verbal input will be required from the participants at certain points of the protocol to continue (cf. Fig. 3b). However, in future iterations, actually artificial intelligence-driven conversation is planned [49], engaging participants in personal questions e.g. about demographic variables in a small talk/rapport module.

As to the appearance of the VEx, a balance will be struck between realism and acceptance – specifically, the design has to avoid the so-called “uncanny valley” [50] describing an aversive perception of almost-but-not-quite realistic artificial agents by human spectators.

### Limitations

The rationale of using the VEx in the context of experimental studies makes the assumptions that the treatment delivery and the accompanying instructions are, in fact, the most important aspects for the generation of PRs. While instructions alone have been shown to effect PEs [5, 51, 52], it has been demonstrated that conditioning paradigms may have better results [6]. However, a conditioning approach was considered too logistically demanding at this stage.

It is possible that the control group itself will not fully believe in the veracity of them only receiving inert medication. However, this would lead to a conservative estimate of placebo effectiveness and is therefore no hazard to the internal validity of the study. We are also considering the option of using a no-treatment control (i.e., no placebo delivery at all) instead of a “control/placebo” instruction.

While evidence exists that female doctors are estimated to have better explanation skills and technical skills and have a higher acceptance [53], the decision to only include male models in the creation of the VEx was made for opportunistic reasons (having a male voice actor available).

On a more general note, while the main intention behind the creation of the VEx is the assessment and abolishment of biases in psychological and medical research, there is a possibility that the use of a virtual agent would induce biases of another sort, such as involving computer (il)literacy or opinions towards technological progress [54]. For example, it is feasible that older participants would have a different response to the VEx’ than younger participants, who will have been exposed to virtual reality technology to a higher extent. On the plus side, there is evidence that participants tend to disclose more personal information to a virtual agent than a human experimenter [55, 56], which may be of relevance with increased interactional capabilities of the VEx. Nevertheless, generalizability will be attempted by using a sample beyond student participants. We are further addressing these issues by post-experiment questionnaires and demographical data about the experience with, and daily use of computers and 3D technology.

Furthermore, the novelty of the simulation may serve to accentuate or alleviate effects which would otherwise be (in)effective. The experience of novelty will be assessed and investigated as a potential moderator of treatment efficacy.

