### Bias reduction and manipulation check

A manipulation check will be performed assessing any doubts or suspicions concerning the treatment allocation or the cover story. Preliminary data indicates that the cover story, including the group allocation, are considered convincing by the participants: 18 of 19 people answered “no” to a post-experimental question asking “Did you at any point find the experimental instructions unconvincing?”.

Allocation to the experimental groups will happen in a room adjacent to the room where the pain measurement takes place, and without insight of the laboratory assistant into the allocation. He or she will therefore be fully blinded to the treatment allocation when performing the retest. Measures will be taken to ensure that allocation is not revealed by the participant: The participant will be asked by the VEx, HEx or audio/text display not to notify the laboratory assistant of their treatment allocation, and the laboratory assistant will document any deviations. Audiovisual recording of the participant/laboratory assistant-interaction will be considered if necessary.

All measurements (except blood pressure and skin temperature) and pain reports will be performed on a computer without communication with the laboratory assistant. Furthermore, the instructions for the continuous pain ratings contain a line to emphasize participant anonymity and non-involvement of the laboratory assistant in data analysis, “This next part is very important: Your ratings will be analyzed by a blinded experimenter only after the session is over. Focus as much as possible on the sensation in your immersed hand, and feel totally free to rate your pain precisely and truthfully. Try not to let my presence or any other thought affect the way you report the sensation, or affect the number of trials you complete.” Also, during the pain measurement, the laboratory assistant will remove himself or herself from the immediate vicinity of the participant to sit down at a table in the participant's field of view, but facing in the same direction as the participant as to not give the participant the feeling of being observed (beyond an initial making sure that all instructions are complied with).

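### Disbelief in the 'inert' instruction is conservative for the overall placebo test, but the protocol wrongly extends that assurance to the whole study, including the VEx–HEx comparison

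*Protocol article*

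**What the plan says.** Three parts of the protocol article bear on this point.

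- **Limitations.** The authors accept that disbelief may occur: "It is possible that the control group itself will not fully believe in the veracity of them only receiving inert medication". They then conclude: "However, this would lead to a conservative estimate of placebo effectiveness and is therefore no hazard to the internal validity of the study". No rate is given, overall or by Metaphor.
- **Hypotheses and expected results.** The PE is a contrast with the control arm: "The PE would be constituted by a larger symptom improvement from Sequence 1 to Sequence 2" under the 'medication' instruction than under the control instruction. On the agents, "a non-significant difference between VEx and HEx would be considered as a first step to establish the viability of the VEx". The closing paragraph, after Figure 4, states the decision: "If we indeed do not find significant differences of PEs induced by the VEx versus an HEx, we will proceed to more complex protocols". The section also says that "The design does not strictly permit the establishment of equivalence between Metaphors in the sense of a non-inferiority trial", and that on a descriptive level "we are expecting a slightly lower effect induced by the VEx".
- **Bias reduction and manipulation check.** Here the plan is: "A manipulation check will be performed assessing any doubts or suspicions concerning the treatment allocation or the cover story". It also cites early data in which 18 of 19 people did not find the instructions unconvincing; the figure is not split by Instruction or Metaphor.

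The section on the Instruction predictor puts the question about assumed drug efficacy to the 'medication' group only.

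**The concern.** A control participant who suspects the pill is active may respond partly as if medicated. This reduces the 'medication' minus 'inert' difference. When the question is whether a PE exists, a reduced difference makes a positive finding harder to reach, so the bias is conservative.

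The VEx–HEx question runs the other way. The quantity compared is the PE, so the control arm enters on both sides, and the favourable result is the absence of a significant difference. A bias that shrinks the gap therefore makes the favourable result easier to reach. If controls believe the inert message to different degrees under the two agents, the gap is distorted in a direction that cannot be known in advance. The stated inference covers the study as a whole, so it covers this comparison too, and there it fails. At stake is whether a similar or different PE under the two agents can be read as telling us about the agents rather than about belief in the control arm.

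**Working it through.** **The plan's own figures.** The target is N = 50 in six groups, or 50/6 = 8.33 per cell. The projected 58 follows from 50 × 1.15 = 57.5, rounded up; dividing instead gives 50/0.85 = 58.8, or 59. The article gives no power, effect size or disbelief rate to reproduce.

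**Model (assumed).** A fraction q of inert-arm participants respond fully as if medicated. With true effects dH and dV:

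- estimated PE = (1 − q) × d
- VEx–HEx gap = (1 − qH)·dH − (1 − qV)·dV = (dH − dV) − (qH·dH − qV·dV)

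With equal q the gap is (1 − q)(dH − dV), which is always shrunk. With unequal q and dH > dV, the gap moves down towards or past zero if qH·dH > qV·dV, and widens if the inequality is reversed.

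**Precision.** Pilot study 2 gives SDs of 15.0 and 15.5, means of 46.4 and 40.8, n = 33 and ICC(2,1) = 0.72. Solving the ICC with the mean shift included gives a correlation of 0.764 and an SD of change of √(15.0² + 15.5² − 2 × 0.764 × 15.0 × 15.5) ≈ 10.5. Taking 0.72 directly as the correlation gives 11.4. Using 10.5:

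- SE of the four-cell gap = 10.5 × √(4/8.33) ≈ 7.3 VAS points
- gap detectable with 80% power = (1.96 + 0.84) × 7.27 ≈ 20.4 points

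**Overall Instruction test** (25 per group, assumed PE 10). With 30% disbelief the estimate falls to 7 and power from 92% to 66%. The protocol's statement is right here.

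**VEx–HEx, equal disbelief.** Chance of a non-significant result (normal approximation, two-sided 0.05 assumed):

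| True PE, HEx v VEx | q = 0 | 0.2 | 0.3 | 0.5 |
|---|---|---|---|---|
| 10 v 5 (gap 5) | 89% | 92% | 92% | 94% |
| 20 v 10 (gap 10) | 72% | 80% | 84% | 89% |
| 20 v 0 (gap 20) | 21% | 41% | 51% | 72% |

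A true gap of 4 points shrinks to 4 × 0.8 = 3.2 or 4 × 0.6 = 2.4 at q = 0.2 or 0.4. Non-significance moves from 91.5% to 92.8% or 93.7%.

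**VEx–HEx, unequal disbelief.**

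- True PE 20 v 10, qH = 0.4, qV = 0.1: gap 12 − 9 = 3; non-significant 93% of the time, against 72% without disbelief.
- Same effects, qH = 0.1, qV = 0.4: gap 18 − 6 = 12; non-significant 62%.
- True PE 8 under both agents, qH = 0.1, qV = 0.3: 7.2 − 5.6 = 1.6 points of spurious HEx advantage; non-significance moves from 95.0% to 94.4%.

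**The case against.** The strongest reply has five parts.

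1. *The protocol does not rest its success on this comparison.* Potential and outlook ties overall success to replicating the PE with the HEx, where attenuation is conservative. Equivalence is disclaimed, and non-significance is called only a first step. This stands as a limit on the point. Even so, the rule for moving to the next stage uses the VEx–HEx result.
2. *The effect is small.* For gaps of 4 to 5 points it is a few percentage points, because about 8 per cell already gives roughly 90% non-significance. This also stands: low precision is the larger problem for that comparison.
3. *Mitigation exists.* The authors are considering a no-treatment control instead of the inert instruction, and a check of doubts is planned. The first would remove disbelief in the inert message but is only an option. The second is where the fix belongs. How its results enter the analysis may properly be left to a fuller plan, and its absence from the article is not criticised here.
4. *Credibility is part of what the agents are being compared on.* This is arguable. But a PE that looks smaller because controls doubted the inert message does not show a weaker 'medication' message.
5. *A requirement that belief be similar would be unworkable.* Agreed. About 8 inert participants per Metaphor cannot show similarity, and uniform disbelief would pass such a check.

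A reader might infer that disbelief pushes the study towards success. The documents do not support that. No rates are given, sufficiently greater disbelief under the VEx widens the gap, and overall success is defined on the HEx replication.

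**Conclusion.** The point holds in a limited form. The Limitations sentence is valid for the overall Instruction test and for the HEx replication, and invalid for comparing PEs between VEx and HEx. Equal disbelief makes the favourable non-significant result more likely; disbelief that differs by Metaphor biases the comparison either way. The net direction is unknown. The size ranges from a few percentage points for true gaps near 5 VAS points to 8–17 points for a gap of 10 (72% to 80–89%), and more for a gap of 20.

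These figures assume equal cells, N = 50, the pilot SD of change, a two-sided 0.05 test, full response among disbelievers, and illustrative PEs and disbelief rates that the article does not supply. With the SD of 11.4 the pattern is the same (76% to 83–90% for a gap of 10).

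**What to change.** - Reword the Limitations sentence: control-arm disbelief is conservative for the overall test of Instruction, and this does not extend to comparisons between Metaphors.
- Within the planned manipulation check, put the same graded item to all six cells: how sure the participant is that the pill was active. Ask it preferably before the retest, for example at the end of the intermission, so that retest pain does not colour the answer.
- Report the item by Metaphor and Instruction.
- Report the VEx–HEx difference in PEs with a confidence interval rather than by significance alone.
- Add a sensitivity analysis that takes inert-arm belief into account, for example by recomputing the gap over a range of qH and qV informed by the ratings. Set no pass/fail threshold for similar belief.

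The cost is one extra rating item, a small risk of prompting suspicion if it is asked before the retest, and a more cautious VEx–HEx conclusion.
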